## Abstract

**Background:**

The oral health of cancer survivors can be compromised by cancer treatment, resulting in reduced treatment efficacy and poorer quality of life. Data suggests that targeting oral health may improve systemic health outcomes in cancer survivors. The Facilitated Lessons on Oral and Systemic Health in Survivors (FLOSS) Project is a 2-arm, 6-month randomized controlled trial (RCT), purposed to answer the research question, “*What is the role of oral telehealth in yielding more favorable oral and systemic health outcomes in cancer survivors*?”.

**Methods:**

Participants (*N* = 100) will be recruited and randomized to the telehealth intervention (THI; *n* = 50) or usual care (UC, *n* = 50) arm. THI participants will engage in six monthly sessions designed to increase oral health-related knowledge and self-efficacy. Sessions utilize motivational interviewing and rely on behavior change techniques including: self-monitoring, goal-setting and implementation planning. Assessments of oral and systemic health outcomes will be conducted at baseline, 6- and 12-months and consist of: intraoral images, blood and saliva collection, and questionnaires to assess quality of life, lifestyle behaviors, and demographics.

**Discussion:**

FLOSS Project is one of the first theory-driven, randomized controlled trials examining the role of oral telehealth in promoting oral and systemic health in cancer survivors and is responsive to national health and research priorities. Successful completion of this project will provide evidence for an accessible intervention to promote oral and systemic health from an integrative lens in cancer survivors, post primary treatment.

**Trial registration:**

ClinicalTrials.gov; NCT06315855. Registered on 03/11/2024.

## Administrative information

Note: the numbers in curly brackets in this protocol refer to SPIRIT checklist item numbers. The order of the items has been modified to group similar items (see http://www.equator-network.org/reporting-guidelines/spirit-2013-statement-defining-standard-protocol-items-for-clinical-trials/).

## Introduction

### Background and rationale {6a}

Disparate rates of poor oral health exist among cancer survivors—in part due to oral complications from cancer treatments (e.g., chemotherapy and oral mucositis). Over 40% of cancer survivors develop oral mucositis (e.g., mouth sores) during treatment. Oral mucositis and other oral complications can lead to treatment delays negatively impacting treatment efficacy and quality of life in cancer survivors [1]. Despite their bidirectional relationship [2], few studies have investigated oral and systemic health outcomes in cancer survivors from a integrative lens. We briefly review the literature on oral and systemic health within cancer survivorship, with the aim of elucidating the potential efficacy of oral health treatment in improving cancer survivorship.

#### Oral and systemic health in survivors

The oral cavity is a microcosm of the human system [hereto referred to as the oral microbiome], showing signs of several systemic health conditions [2]. The oral microbiome contains upwards of 2,000 microorganisms that symbiotically promote the oral health of an individual (e.g., homeostasis). A disruption to oral homeostasis, (i.e., oral dysbiosis) can lead to the development of oral disease (e.g., periodontal disease), by way of inflammation [3]. Inflammation is one central biological pathway by which oral health impacts systemic health, as oral microbiota may enter the circulatory system (via distressed tissue), respiratory system (through aspiration) or gut system (through the digestive tract) [3]. For cancer survivors, cancer therapies disrupt oral homeostasis leading to tissue destruction and inflammation. Periodontitis is a chronic inflammatory disease that not only increases cancer incidence risk by 122% [4] but is also prevalent in cancer survivors [5]. Vargas-Villafuerte and colleagues (2016) examined inflammation among patients with and without breast cancer following periodontal treatment. Results indicated that treatment of periodontal disease substantially improved inflammation (as evidenced by reduced CRP levels) in patients without cancer; however, periodontal treatment in cancer survivors did not yield a significant reduction in inflammation, suggesting that cancer survivors may need additional oral health promotion and treatment beyond standard of care for non-cancer patients [6].

In addition to inflammation as a biological pathway impacting systemic health in survivors, modifiable behavioral risk factors (e.g., diet) link oral and systemic health outcomes by altering the oral microbiome. For example, data from NHANES 2005–2016, show that cancer survivors report suboptimal diet quality [7], which is linked with increased risk for chronic comorbidities (e.g., diabetes) and mortality [8]. Nutrient-rich and nutrient-diverse diets that are low in sugar, high in fiber, and high in omega-6 to omega-3 fatty acid ratio can reduce risk of periodontal disease by diversifying oral microbiota and aiding in maintaining oral homeostasis [9]. Addressing biological and behavioral pathways that inform oral and systemic health in cancer survivors has potential to improve overall health and quality of life in cancer survivors.

#### Oral health and quality of life

Oral health problems can significantly impact quality of life (i.e., oral health related quality of life) yielding functional limitation, physical pain, psychological discomfort, physical disability, social disability etc. [10]. Jardim and colleagues examined oral health and oral health-related quality of life in a sample of 151 breast cancer survivors and found that xerostomia (i.e., dry mouth) and 3 or more filled teeth were associated with a 2.92-fold and 1.98-fold greater odds of having a lower oral-health related quality of life, compared to women without dry mouth and a smaller number of filled teeth [11]. These findings demonstrate that oral health promotion has potential to improve quality of life in cancer survivors (e.g., daily functioning including chewing, swallowing).

Taken together, studies demonstrate an association among oral health (e.g., treated periodontal disease) cancer incidence and morbidity, and quality of life in cancer survivors. Current literature and evidence-based trials to improve oral health outcomes in cancer survivors have predominantly focused on head and neck cancer sites [12]. There is an urgent need to address the oral health needs of non-head and neck cancer survivors in order to improve quality of life.

### Objectives {7}

To enhance quality of life among cancer survivors, solutions that address risk factors integral to oral and systemic health are needed. Although basic oral protocols are recommended as part of oncology patient care [1], cancer survivors may benefit from additional support outside of the clinical setting to promote long-term oral and systemic health. Oral telehealth—technology-supported oral health promotion—is an effective and accessible oral health promotion tool used outside of the clinic. Oral telehealth has shown efficacy in reducing plaque and gum swelling [8], yet is an underutilized tool for oral health promotion particularly among cancer survivors. Few studies have systematically examined the efficacy of oral health promotion in improving systemic health outcomes in cancer survivors [2, 7]; and no studies—to our knowledge—have used a randomized controlled trial design. Moreover, prior oral telehealth studies have not been theory-driven and lack fidelity monitoring of treatment protocol [1].

### Trial design {8}

Facilitated Lessons on Oral and Systemic Health in Survivors (FLOSS) is a 2-arm, parallel group, 1:1 allocation, superiority randomized controlled trial.

## Methods: participants, interventions and outcomes

### Study setting {9}

Study procedures including assessments will take place in community-based research office. Intervention delivery will occur via telehealth platform, Teledent. Data collection will occur in Washington, DC Metropolitan area within the Mid-Atlantic region of the US.

### Eligibility criteria {10}

The study population will comprise 100 unselected cancer survivors, recruited via established community-based approaches. “Unselected’ cancer survivors refer to individuals not selected based on cancer type. With the exception of head and neck cancer, all other cancer sites are eligible for this study. Survivors will be identified via cancer survivorship groups and established community-based approaches (e.g., community outreach programming). The inclusion criteria are: (1) male and female cancer survivors who ≥ 6 months after completion of primary therapy for cancer treatment; (2) greater than 25 years of age, and less than 75 years of age; (3) all race/ethnic groups; and (4) own a smart phone. The exclusion criteria include the following: (1) all head and neck/oral cancers; (2) less than 25 years of age and greater than 75 years of age; (3) recurrence/second cancers; and (4) unable to provide informed consent.

### Who will take informed consent? {26a}

Trained research personnel, including a postdoctoral research fellow and graduate students will obtain informed consent from potential trial participants.

### Additional consent provisions for collection and use of participant data and biological specimens {26b}

Eligible participants are informed of biospecimen collection, handling, and storage as part of the consenting procedure for all study activities. Study personnel inform participants that saliva samples will be self-collected and blood samples will be collected by a trained phlebotomist. In addition, study personnel share that samples will be de-identified, transported by a courier, and processed and stored at the Tissue Culture and Biobanking Shared Resource at Georgetown University. Written consent is obtained on the consent form for the collection of biospecimen. At the time of biospecimen collection, study personnel obtain verbal consent from participants for both saliva and blood samples. The collection of biospecimen for each participant is documented by study personnel and saved within the participant record.

## Interventions

### Explanation for the choice of comparators {6b}

Oral telehealth has shown clinically significant reductions in plaque, gingival inflammation, and the incidence of mouth sores (i.e., white lesions from oral mucositis), compared to conventional approaches [13]. Thus, its selection as a choice comparator is justified. While prior interventions have used asynchronous approaches, many have lacked personalization. This trial uses a synchronous approach to provide tailored feedback to aid individual participants in attaining the oral health goals.

Participants in the usual care arm will receive biweekly text messages which provide general health information and recommended practices about oral and systemic health.

### Intervention description {11a}

The intervention is grounded in social-cognitive theory, which posits that human behavior is mutually-influenced by person- and environmental-level factors [9]. The FLOSS project is a 6-month telehealth intervention (THI) that provides education on cognitive, behavioral and environmental-level factors that inform oral and systemic health. Participants randomized to THI arm will engage in 6, monthly 1-h virtual sessions with a facilitator training in motivational interviewing. Each session will contain: 1) a participant check-in, 2) content designed to build oral health literacy and self-efficacy, 3) and goal-setting and implementation planning. Participants will complete module handouts on-paper or electronically that reinforces module content. Additionally, participants will also receive biweekly tailored text messages aligned with monthly module content. Post-intervention follow-up will occur at 6- and 12-month post-randomization. See lineup of module topics below:

**Table Tabb:** 

Module Topic	Content
1. Connecting Oral and Systemic Health	Relationship between oral health and cancer outcomes Proper Brushing Technique Using Bass Method
2. Social Determinants of Oral Health	Common risk factors linking oral and systemic health Proper Flossing Technique
3. Diet and Oral and Systemic Health	Sugar and Oral Microbiome Healthy Hydration
4. Smoking and Alcohol and Oral and Systemic Health	Effects of Smoking on Oral and Systemic Health
5. Cancer Survivors, Oral and Systemic Health	Unique Oral Health Experiences of Cancer Survivors Managing Pain/Discomfort
6. Implementation for Long Term Maintenance	Completing Action Plan for Behavior Maintenance Celebrating Successes Exit Interview

### Criteria for discontinuing or modifying allocated interventions {11b}

Participants can withdraw from either study arm voluntarily. Participants randomized to the telehealth intervention group who wish to withdraw from the study will receive the intervention module materials via email or print. We will collect assessment data from participants who discontinue the intervention.

### Strategies to improve adherence to interventions {11c}

Fidelity monitoring is ongoing to assess treatment fidelity. Facilitators whose adherence to protocol is suboptimal will undergo additional protocol training.

### Relevant concomitant care permitted or prohibited during the trial {11d}

Treatment for cancer is prohibited during the trial. Participants cannot be undergoing treatment.

### Provisions for post-trial care {30}

This study does not have provisions for post-trial care. Participants will receive a 6-month report of progress pre- and post-intervention.

### Outcomes {12}

#### Primary outcomes

Primary outcomes of interest are related to oral health, including image-rated oral mucositis image-rated gingival inflammation and quality of life. We will also capture self-reported oral mucositis and gingival inflammation via survey (using Qualtrics Online Survey Platform [18]). Our target endpoint is 6-months, post-randomization.

##### Intraoral Imaging

All participants, prior to randomization will undergo an intraoral imaging assessment. Intraoral imaging will be conducted on all study participants at the time of their baseline in-person visit using Mouthwatch® intraoral cameras. Photos of the mouth, teeth, and gums will be captured and saved in individual patient files for research and data purposes only. Images will be captured at 6- and 12-month follow-up assessment visits. We will have a dental consultant review the images and provide summary data. The World Health Organization oral mucositis toxicity scale will be used to assess oral images. The WHO Oral Toxicity Scale rates the anatomical, and function aspects of oral mucositis. The severity of oral ulcers and ability to consume food and liquid is reported on a scale of 0 (no presentation of symptoms) to 4 (not able to tolerate food or liquid diet). Higher scores indicate worse oral mucositis symptomology. To assess gingival inflammation, the Modified Gingival Index will be applied to intraoral images. We will rate inflammation of the gums on a 5-point Likert Scale ranging from 0 (absence of inflammation) to 4(severe inflammation, marked redness, edema. Higher scores indicate more severe inflammation.

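### Image-rated oral mucositis, a primary outcome, cannot be fully graded from photographs on a scale that includes eating function, and a floor effect is likely in people at least 6 months past treatment

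*Protocol article*

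**What the plan says.** The Primary outcomes section names "image-rated oral mucositis image-rated gingival inflammation and quality of life" and adds: "Our target endpoint is 6-months, post-randomization". Under Intraoral Imaging, photographs of the mouth, teeth and gums are taken at each visit and reviewed by a dental consultant. For mucositis, "The World Health Organization oral mucositis toxicity scale will be used to assess oral images". The same paragraph says that the scale rates anatomical and functional aspects: "The severity of oral ulcers and ability to consume food and liquid is reported on a scale of 0" (no symptoms) up to 4, where 4 means that neither food nor a liquid diet is tolerated.

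On who is studied:
- The rationale states: "Over 40% of cancer survivors develop oral mucositis (e.g., mouth sores) during treatment".
- Eligibility admits "male and female cancer survivors who ≥ 6 months after completion of primary therapy for cancer treatment". It excludes head and neck cancers and recurrent or second cancers, and sets no minimum mucositis score at baseline.
- The concomitant care section states: "Treatment for cancer is prohibited during the trial".
- The missing-data section removes from the final analyses anyone with a new or recurrent cancer during the intervention.

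PROMS, a 15-item self-report mucositis scale, includes an item on eating hard foods. It is described as a separate self-report measure and does not appear in Table 1.

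**The concern.** There are two problems, and they differ in strength.

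**Instrument and data source.** The outcome is called image-rated, the rater works from images, and the protocol's own description of the scale contains a component that an image does not hold. Either the rater guesses eating function, or grades on the lesion alone and reports something other than the named scale, or draws on an unnamed source. Each choice gives a different primary outcome, and the choice could vary between visits.

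**Likely floor.** The rationale ties mucositis to treatment, while the eligibility and analysis rules together restrict the analysed population to people who are off treatment and at least 6 months past it. If most scores are 0 at baseline and at 6 months, this primary outcome has little room to separate the arms. A null result could be misread as no benefit to oral health, and would feed into the larger trial that these results are meant to help size. Under a Bonferroni correction it would also lower the power of the other primary outcomes.

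**Working it through.** **1. Grade against source (no arithmetic).** Scale content as described: ulcer severity, plus ability to consume food and liquid. Rater's input as described: photographs. The first part is visible and the second is not. No section passes PROMS, or any other eating question, to the rater or into the grade. The article describes only the two ends of the scale. Grade 4 is shown to be functional, but what separates grades 1 to 3 is not stated.

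**2. The plan's own sample size.** Inputs from the Sample size section: d = 0.60, 80% power, alpha 0.05 (two-sided reproduces Table 3), 10% attrition. A two-sample t-test needs 45 per arm (power 80.4%), and 45 / 0.90 = 50. The stated 45 and 50 per arm reproduce. The effect size behind them comes from a quality-of-life result only.

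**3. Power for mucositis if the score sits near zero.** Inputs: 45 evaluable per arm. Alpha is 0.05 / 3 = 0.0167, assuming that the Bonferroni family is the three named primary outcomes. The prevalences of a non-zero score are assumptions, because the article gives no post-treatment rate. The score is coded 0 versus non-zero, which ignores differences among the higher grades.

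A hand check for the case where the telehealth arm has no events: the two-sided Fisher p-value for k of 45 versus 0 of 45 is 2 × C(45,k) / C(90,k).
- k = 6: p = 0.026
- k = 7: p = 0.012

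At least 7 affected usual-care participants are therefore needed at alpha 0.0167. The probability of 7 or more out of 45 is 0.007 at 5% prevalence, 0.159 at 10%, 0.522 at 15% and 0.823 at 20%.

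| Usual care vs telehealth | Fisher, 0.0167 | Fisher, 0.05 | t-test on 0/1 score, 0.0167 |
|---|---|---|---|
| 5% vs 0% | 1% | 2% | 2% |
| 10% vs 0% | 16% | 29% | 29% |
| 15% vs 0% | 52% | 69% | 69% |
| 20% vs 0% | 82% | 91% | 91% |
| 10% vs 5% | 3% | 6% | 5% |
| 20% vs 10% | 9% | 18% | 14% |
| 40% vs 20% | 30% | 46% | 37% |

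The standardized difference for a 0/1 score is d = (p − q) / √[(p(1−p) + q(1−q)) / 2]. For 15% vs 0% it is 0.59, so the design value of 0.60 needs about 15% affected in usual care and complete elimination in the telehealth arm. For 40% halved to 20%, where 40% is about the rationale's during-treatment figure, d is 0.45.

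**4. Cost to the other primary outcomes.** Two-sample t-test, d = 0.60, 45 per arm:
- Four tests (0.0125): 61.7%
- Three tests (0.0167): 65.7%
- Two tests (0.025): 71.4%

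Removing mucositis moves each remaining outcome from 66% to 71% if the family is three, or from 62% to 66% if it is four.

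**The case against.** The protocol does give a reason for measuring mucositis: the choice-of-comparators section says that oral telehealth has reduced the incidence of mouth sores. A low baseline also does not rule out a difference between arms in new lesions. Both points stand, and with no post-treatment rate in the document a floor is an expectation and not a finding.

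A reader might go further and infer any of the following, none of which the document supports.
- *Scores will be almost all zero, so the outcome can hardly show a difference.* The table does not bear this out across the assumed range: power is 52% for 15% vs 0% and 82% for 20% vs 0%. Those cells require complete elimination, which is optimistic, but they belong in the range.
- *Mucositis takes exactly a third of the alpha.* The Bonferroni sentence does not define its family. Oral-health quality of life has two instruments, so four tests is an equally fair reading.
- *All the upper grades are unscorable.* Only grade 4 is described in functional terms.
- *Gingival inflammation as sole lead outcome would have 80% power.* The value d = 0.60 comes from quality of life. No expected effect, baseline distribution or entry minimum is given for gingival inflammation, so a floor is not excluded there either.

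Finally, recruitment began in May 2024, and demoting a declared primary outcome mid-trial has a credibility cost. That argues for making the measurement correction first and treating demotion as conditional.

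**Conclusion.** The mismatch between instrument and source holds on the text alone: a primary outcome is to be graded from photographs on a scale that the protocol says includes eating function, and nothing supplies that part to the rater. It should be corrected.

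The floor is likely but not demonstrated. Its direction follows from the rationale, the eligibility criteria, the ban on cancer treatment and the exclusion of new or recurrent cancers. Its size depends on an unknown prevalence: power at alpha 0.0167 runs from 1% (5% vs 0%) to 82% (20% vs 0%), and does not exceed 30% in any halving scenario examined. These figures assume 45 per arm, a 0/1 score and a family of three tests. The cost to each other primary outcome is about 4 to 6 percentage points of power at d = 0.60, depending on the family.

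**What to change.** 1. Score the images only on what they show (erythema or ulcer, present or absent). Analyse the proportion with any lesion by an exact test.
2. Take the functional component from the PROMS eating items, and add PROMS to the Table 1 visit schedule so that it is collected alongside the images.
3. Review the baseline images pooled across arms, blinded to allocation. If nearly all scores are 0, consider moving mucositis to secondary or descriptive status. Base this decision on pooled baseline data only.
4. State which tests form the Bonferroni family, so that the effect of step 3 on the remaining primary outcomes is known. Do not claim 80% power for gingival inflammation on the strength of d = 0.60.

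Cost: a protocol amendment and registry update while recruitment is under way, and a lesion score that is no longer the full WHO grade. The images and PROMS are both already planned, but the timing of PROMS has to be fixed.

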#### Self-report oral health measures

##### Oral Mucositis

The 15-item Patient Reported Oral Mucositis Scale (PROMS) will be used to examine participant experiences of oral mucositis. Respondents indicate experiences with oral mucositis on a variety of scales ranging from no experience of a mucositis-related symptoms to complete experience of symptoms. Example items include: *In the past week, have you had difficulty eating hard foods because of mouth sores.* In a validation sample, the PROMS scale was internally consistent (*α* = 0.86).

